### Sample size

At the study design stage, the funder advised that a minimum of 280 mainstream schools would be available to be randomised. Assuming an average of 925 students per school, an average base rate of 12.6 s.47 enquiries per 1000 students per school year under usual practice conditions, and a between-school coefficient of variation of 0.45 within LAs (these estimates are all based on comparator school data from the three pilot studies in Lambeth, Stockport and Southampton) [4], randomising 140 mainstream schools to each group provides 90% power to detect a decrease in rates from 12.6 to 10.48 per 1000 pupils per school year (i.e. a rate ratio of 83.2%). This is using a two-sided 5% type I error level when using a Poisson regression model accounting for cluster randomisation [8].

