#### CSC data

Data sharing agreements will be set up between LAs (Data Controller) and Cardiff University to enable sharing of data related to CSC. Data fields will be included in this data sharing agreement, data will contain no identifiers except for a school ID and/or trial allocation. A data lead will be identified at each LA, and the trial data manager will liaise with each data lead to confirm required fields. Building on our learning from the pilot, each LA will pilot data transfer during the set-up phase to ensure the data can flow and is in the correct format. These checks will be detailed in the data management plan. Once any issues are addressed in this pilot, data will be shared quarterly up to the end of the intervention (July 2022). A final data extract will be requested Summer 2023 for the days in care outcomes. Data will be reported by school year group and by month and provided to the Cardiff team in a proforma developed and agreed during the pilot. Data will be aggregated, and no individual-level data will be sent. These data will be securely transferred to Cardiff University and checked by the data manager. All data will be stored on Cardiff University servers in restricted folders available only to those on the trial team who require access. This will be detailed in the delegation log.

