### Statistical methods

#### Statistical methods for primary and secondary outcomes

All primary analyses will be ‘intention to treat’ i.e. schools will be analysed in the groups to which they were randomised, regardless of adherence to the intervention. Missing outcome data will not be replaced. For the primary outcome analysis, a quasi-Poisson regression model will be fitted with fixed effects for LAs and cluster robust standard errors reflecting the clustering structure (schools within LAs) to compare rates of s.47 enquiries at 23 months by arm, using the number of students per school as the exposure scaling variable, and s.47 enquiries for 2018/19 (baseline) and % eligible for FSM as fixed-effect covariates. Using a quasi-likelihood model accounts for possible over- or underdispersion i.e. variance in the data that is higher or lower than expected under the standard Poisson model. Allocation will be included in the model as a fixed effect, and the intervention effect (model coefficients transformed into rate ratios) will be presented as point estimate with two-sided 95% confidence interval (CI) and p-value. If the estimated rate is lower in the SWIS arm than in the comparator arm and the 95% CI around the estimated rate ratio excludes the null effect (rate ratio = 1), effectiveness of SWIS at the 5% level will be concluded.

Secondary outcomes will be analysed in a similar way as the primary outcome, by fitting regression models with cluster robust standard errors depending on the type of outcome: quasi-Poisson for rates (referrals to CSC, s.17 assessments) and linear for continuous variables (days in care, educational attendance and attainment). For the school-level variables (referrals to CSC, s.17 assessments, days in care) we will include the same fixed-effect covariates in the model as for the primary outcome (allocation, LA, baseline outcome from 2018/19, % eligible for FSM) and also use the number of students per school as the exposure scaling variable. For the student-level variables (educational attendance and attainment) we will additionally include gender and ethnicity as covariates, and the baseline outcomes used will be 2018/19 attendance (for attendance) and KS4 results (for attainment). The p-values generated from the secondary outcome analyses will be adjusted for multiplicity using Hochberg’s step-up procedure.

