### Amendments to the study

The study was extended twice by the funder, first in August 2021, and then in January 2022.This protocol was amended to accommodate the new timeline. This document reflects the amended study design. Both the original protocol (version 1) and the revised protocol (versions 2 and 3) can be found on the OSF. Key amendments made in the updated protocols are:

Timing of analysis and reporting updated to reflect the extended intervention period (e.g. meaning that the main impact analysis will now be published in January 2023 rather than 2021, and the follow-up analysis and final report will now be published in January 2024 instead of June 2022).Changes to the data collection activities in the IPE, to reflect the fact that all case studies were forced online by the pandemic and conducted remotely. This meant that as of September 2021 no observations or child interviews have taken place, and these are now scheduled for terms 4 and 5.Additional data collection activities in the three extra terms, e.g. interviews with key decision makers in LA ‘front door’ teams.The use of the 2018/19 school year as a baseline, rather than the 2019/20 school year as originally planned. This is because the 2018/19 year is the most recent year not affected by the Covid-19 pandemic and therefore a more realistic baseline to use.Changes to the economic evaluation to reflect discounting to costs beyond 12 months from the start of the intervention, to present values using nationally recommended discount rates.

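### The primary model adjusts for one year of s.47 counts only; other pre-trial baselines, two of them already planned, could sharpen it at low cost, by an amount the protocol does not allow one to fix

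*Protocol article*

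**What the plan says.** Under Statistical methods for primary and secondary outcomes, the primary model is a quasi-Poisson regression with fixed LA effects, pupil numbers as the exposure, and "s.47 enquiries for 2018/19 (baseline) and % eligible for FSM as fixed-effect covariates". Referrals and s.17 assessments are each modelled with their own 2018/19 baseline, so those baselines are planned to be held, but they do not enter the primary model.

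Amendments to the study explains that 2018/19 replaced 2019/20, the baseline first planned: "This is because the 2018/19 year is the most recent year not affected by the Covid-19 pandemic". The reason is given for the year as a whole. The months of 2019/20 before the pandemic are not discussed.

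On the form of the LA returns, CSC data states: "Data will be reported by school year group and by month".

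The Sample size section gives "an average base rate of 12.6 s.47 enquiries per 1000 students per school year under usual practice conditions", a between-school coefficient of variation of 0.45 within LAs, and "Assuming an average of 925 students per school". It takes no credit for baseline adjustment.

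**The concern.** The baseline covariate is there to remove stable differences between schools from the comparison. A baseline that is itself a small count does this only partly, because chance variation in one year's enquiries dilutes its link with the outcome. Two sources of extra information lie close at hand: the 2018/19 referral and s.17 counts, and the s.47 counts from the start of 2019/20, which are a year nearer to the outcome window. Both precede 2 September 2020, so the intervention cannot have affected them, and adjusting for them introduces no bias. At stake is the width of the confidence interval for the primary rate ratio, not its validity.

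**Working it through.** **The plan's own figure.** With rates 0.0126 and 0.01048, k = 0.45 and 925 pupils, the standard formula for cluster-randomised rates is c = 1 + (z_a + z_b)² × [(l0 + l1)/y + k²(l0² + l1²)]/(l0 − l1)². For one school year, the bracket over (l0 − l1)² is (0.00002495 + 0.00005439)/0.000004494 = 17.65. This gives 139.6 schools per arm at 80% power and 186.5 at 90%. With two years of follow-up, 140 per arm has 86.4% power. The stated 90% is therefore not reproduced. That is a separate matter: the formula contains no baseline term, so nothing below depends on it.

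**Reliability of the baseline.** The expected 2018/19 count is 925 × 0.0126 = 11.66 per school, with sampling variance on the log scale of about 1/11.66 = 0.0858. Reliability is 0.2025/(0.2025 + 0.0858) = 0.70. With six further months, taken as half a year, it is 0.2025/(0.2025 + 0.0572) = 0.78.

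**Gain from the extra months.** Assumptions not in the protocol: September 2019 to February 2020 is unaffected by Covid-19; true school log rates have variance 0.2025 and a correlation rho between adjacent years that decays with distance; a pandemic break multiplies all pre/post covariances by b. The outcome covers two school years.

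Worked case, rho = 0.8 and b = 1:

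- Outcome variance: 0.2025 × (1 + 0.8)/2 + 0.0858/2 = 0.2252.
- Covariance with 2018/19: 0.2025 × (0.64 + 0.512)/2 = 0.1166.
- Residual variance with 12 months: 0.2252 − 0.1166²/0.2883 = 0.178.
- 18 months pooled (weights 2/3 and 1/3): covariance 0.1264, variance 0.2417, residual 0.2252 − 0.1264²/0.2417 = 0.159.
- Reduction 10.6%, worth 280 × (0.1780/0.1591 − 1) = 33 schools.

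Other values, as reduction (extra schools):

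| rho | b = 1 | b = 0.7 | b = 0.5 |
|---|---|---|---|
| 0.95 | 14.4% (47) | 4.9% (15) | 2.2% (6) |
| 0.9 | 13.2% (43) | 5.0% (15) | 2.3% (7) |
| 0.8 | 10.6% (33) | 4.6% (13) | 2.2% (6) |
| 0.7 | 8.0% (24) | 3.7% (11) | 1.8% (5) |
| 0.5 | 3.7% (11) | 1.8% (5) | 0.9% (3) |

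Entering the two periods as separate covariates instead of pooling them does slightly better in the same model (10.8-14.7% at rho 0.7-0.95, b = 1). A simulation of the quasi-Poisson model with LA effects agrees with the b = 1 column. At rho 0.95, 0.9, 0.8 and 0.7, the standard deviation of the log rate ratio falls from 0.0463 to 0.0426, 0.0517 to 0.0476, 0.0541 to 0.0512 and 0.0569 to 0.0544, which is 9-15% in variance.

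If both baseline periods are instead given the same correlation r with the outcome, so that being a year nearer brings no benefit, the extra months (6 of 11) are worth 5, 13, 19 and 28 of 280 schools at r = 0.5, 0.7, 0.8 and 0.9.

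**Gain from the referral and s.17 baselines.** The protocol gives neither their rates nor their correlation q with s.47. Taking them as 5 and 3 times as frequent as s.47, mutually correlated at q, with b = 1, the reduction runs as follows for q from 0.3 to 0.9: under 1% throughout at rho = 0.5; 0.5-6.2% at rho = 0.8; 1.5-19.8% at rho = 0.95. If both are only twice as frequent, the top value is 17.7%.

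**The case against.** The choice of 2018/19 is reasoned and contradicts nothing: it is the last full year before the pandemic. No stated power depends on it. This stands, and it is why the point is not an error.

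A reader might infer that the plan loses precision worth tens of schools. The document does not support that. The larger values need high yearly correlation and no break across 2020, and the Discussion itself warns that outside factors may override the intervention and that some indicators may not be comparable with earlier years. The planned model also includes % FSM, which the simulation did not. If FSM removed half the within-LA variance (an assumption), the gain at rho 0.7-0.95 with no break would fall to 5.5-10.3%. In terms of power the effect is small: under the common-correlation model, the extra months move it from 0.915 to 0.920 at r = 0.5 and from 0.972 to 0.980 at r = 0.8.

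A reader might also infer from the monthly reporting that the 2019/20 months are already in hand. They may not be. The sentence quoted from CSC data sits in a description of transfers during the trial. Other secondary analyses treats even monthly outcome data as conditional on availability, and data fields are tied to each LA's sharing agreement. That 2019/20 was once the planned baseline does not show that it was collected.

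Finally, pooling 18 months into one baseline would be awkward. Each child is coded 0/1 within a window and only aggregates are sent, so the team could not itself remove children counted in both periods. The fix below avoids this.

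**Conclusion.** The point holds as a conditional efficiency gain. The primary model uses one outcome baseline with reliability of about 0.70 on the protocol's inputs, leaves out two baselines that the trial already plans to hold, and sets aside the pre-pandemic part of 2019/20 on a reason that does not apply to it. The extra months would cut the variance of the log rate ratio by about 8-14% in favourable conditions and about 1-5% with a marked break or low correlation. The referral and s.17 covariates would add from near zero to roughly 17-20%, the top end needing both a very stable school rate and very closely related outcomes. All these sizes rest on correlations and frequencies that the protocol does not give, and FSM adjustment may shrink them. Validity, the type I error rate and the stated sample size are untouched. No calculation supports carrying the idea over to attendance or to the other social care outcomes, so it is not recommended for those.

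**What to change.** Before outcome data are analysed, pre-specify two additions to the primary model:

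- The school's 2018/19 referral and s.17 rates as covariates. These are already planned for the secondary models, so the cost is analysis-plan wording and two degrees of freedom among 280 schools.
- Where LAs can supply it, the school's s.47 rate for September 2019 to February 2020, as a separate covariate with that year's roll as its denominator. Keeping it separate from 2018/19 means that children need not be de-duplicated across the two periods. Where an LA cannot supply it, keep 2018/19 alone and state in advance how those schools are handled.

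The second addition needs a further retrospective request to the LAs, which the data sharing agreements may have to cover. If the sponsor judges that not worthwhile, the first addition can stand alone, with a sentence saying why the pre-pandemic months of 2019/20 are not used.

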#### Other secondary analyses

A secondary analysis will use per-term (or per-month, if available) outcome data and include term (or month) as an additional covariate in the model to explore potential implementation effects and/or seasonality. Another secondary analysis will assess the hypothesised mediators of change outlined in logic model (S1 Appendix) at the 23-month follow-up by fitting an interaction term between allocation and category of implementation fidelity (a Gold, Silver, Bronze categorisation will be developed based on a re-analysis of pilot data and other insights from the IPE). Any other subgroup analyses (e.g. by age group) will be agreed with service user input. The p-values generated from these secondary and subgroup analyses will also be adjusted for multiplicity using Hochberg’s step-up procedure. We will fit a two-level mixed-effects model with random LA effects as an additional robustness analysis.

Missing outcome data will not be replaced in the primary analysis, but we will perform null imputation for missing covariates, where we will replace missing values with 0, and create a dummy indicator for the covariate coded 1 if the value was missing, and 0 otherwise, and include the dummy in the regression. If more than 5% of outcome data are missing, we will consider repeating the primary analysis after multiple imputation. To assess the impact of non-compliance (if present), we will exclude intervention arm schools that did not adopt the intervention at all and then repeat the primary analysis, and we will also perform a complier average causal effect (CACE) analysis. Statistical code and anonymised data can be provided upon reasonable request, in line with Centre for Trials Research policy.

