### Strategies to improve adherence to interventions

We anticipate good adherence to the intervention, as the funding for the trial intervention (i.e. the social worker) is provided to participating LAs and schools on the basis of compliance with the intervention guide supplied by the funder, and LAs have committed to delivering SWIS as described. All schools also confirmed their commitment at the outset. However, the adverse circumstances of Covid-19 may mean that some sites need to adapt SWIS, for example to accommodate social distancing or increased remote working. The IPE is designed to capture such adaptation and secondary analyses will explore the impact of varied levels of adherence.

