### Outcomes

#### Primary outcome

*Child protection (Section 47) enquiries*. Child protection (s.47) enquiries are investigations CSC carry out when they have “reasonable cause to suspect that a child who lives, or is found, in their area is suffering, or is likely to suffer, significant harm” (Children Act, 1989). This is a key point in the work of CSC; an enquiry would normally involve an assessment of the child’s needs and the ability of family members or carers to meet them. Social workers would normally interview family members, children (if they are old enough), and use information from other agencies such as schools and health. This data will be collected from LA CSC departments, based on a data sharing agreement between each LA and the research team.

Child protection (s.47) enquiry starts will be recorded as a binary (no enquiry/ enquiry started) variable. If the s.47 start date lies between and including the start date of the academic year (2nd September, 2020), and 31st July 2022, it will be coded 1, otherwise it will be coded 0. Enquiries will be recorded at the individual-level, then aggregated at the school-level and shared with the research team. This aggregated count variable will be our outcome measure.

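### Term (or month) entered only as a main effect describes seasonality but cannot show whether the SWIS effect changes over time

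*Protocol article*

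**What the plan says.** In the Protocol article, Other secondary analyses, outcome data by term (or by month where available) are to be modelled so as to "include term (or month) as an additional covariate in the model to explore potential implementation effects and/or seasonality". The sentence after it, on the logic-model mediators, does name an interaction: "fitting an interaction term between allocation and category of implementation fidelity".

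The model to which term is added is given under Statistical methods for primary and secondary outcomes: "a quasi-Poisson regression model will be fitted with fixed effects for LAs and cluster robust standard errors", "using the number of students per school as the exposure scaling variable", with "s.47 enquiries for 2018/19 (baseline) and % eligible for FSM as fixed-effect covariates". As written, each of these terms, and the exposure, takes one value per school.

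Two statements on the data matter here. Under Primary outcome, "Child protection (s.47) enquiry starts will be recorded as a binary (no enquiry/ enquiry started) variable", with a single window from 2 September 2020 to 31 July 2022. Under CSC data, "Data will be reported by school year group and by month".

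**The concern.** In regression language an additional covariate is a main effect. The document does not define implementation effects. The natural reading in an analysis by period is that SWIS may have worked differently in early, Covid-affected or later terms, and that is a difference between arms that varies with time. A term effect common to both arms cannot represent it.

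Such change is plausible in this trial. The adherence section says that "the adverse circumstances of Covid-19 may mean that some sites need to adapt SWIS", and the two extensions added three terms to the intervention. Among the analyses described, this is the only one that uses calendar time. If it is run as worded, a report could say that implementation effects over time had been explored when the allocation estimate was little more than a repeat of the primary result.

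**Working it through.** The protocol gives no figure for this analysis, so there is none to reproduce. The check is algebra, then a numerical confirmation.

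**1. What the stated model can estimate.** For school *i* and term *t*, let `Y_it` be the count, `N_i` the student count, `A_i` the allocation, `z_i` the other school-level covariates (LA, 2018/19 baseline, % FSM) and `g_t` the term effect:

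`log μ_it = log N_i + a + θ·A_i + z_i'b + g_t`

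The rate ratio between arms in term *t* is `exp(θ)` for every *t*. The change in log rate ratio between any two terms is θ − θ = 0 by construction. With an interaction, the log rate ratio in term *t* is `θ + δ_t`. The stated model sets every `δ_t` to zero.

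**2. Relation to the primary estimate.** Let `x_i` collect the intercept, `A_i` and `z_i`, with coefficients `β`. The Poisson (and quasi-Poisson) estimating equations for `β` are

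`Σ_i x_i Σ_t (Y_it − N_i·exp(x_i'β + g_t)) = 0`

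Write `G = Σ_t exp(g_t)` and `Y_i = Σ_t Y_it`. Then

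`Σ_i x_i (Y_i − N_i·G·exp(x_i'β)) = 0`

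This is the aggregated model with its intercept shifted by `log G`, so `θ` is the same. The step needs (a) every school to have every period, so that `G` is common; (b) one `N_i` per school; and (c) period counts that sum to the 23-month count.

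**3. Numerical confirmation.** Taken from the protocol: 280 schools, 12.6 enquiries per 1000 students per school year, and a between-school coefficient of variation of 0.45. Assumed: 20 LAs of 14 schools, school sizes from 500 to 1400, six terms with seasonal factors 1.2, 1.0, 0.8 in each year, and rate ratios by term of 1.00, 0.95, 0.85, 0.75, 0.65, 0.60. Standard errors were clustered on school. The assumed time-averaged rate ratio is (1.20 + 0.95 + 0.68 + 0.90 + 0.65 + 0.48)/6 = 4.86/6 = 0.81. There were three datasets per scenario:

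| Scenario | Primary RR vs term-main-effect RR |
|---|---|
| All three conditions hold | 0.81833419 vs 0.81833419; 0.85750539 vs 0.85750539; 0.84586458 vs 0.84586458 |
| Student count varies by about 3% across terms | 0.8055 vs 0.8057; 0.8765 vs 0.8756; 0.8506 vs 0.8497 |
| 5% of school-terms missing | 0.8183 vs 0.8209; 0.8575 vs 0.8675; 0.8459 vs 0.8483 |
| Child counted once over 23 months but once per term in term data (strong repeat risk assumed; term sums 7–9% above the aggregate) | 0.850 vs 0.835; 0.813 vs 0.803; 0.804 vs 0.796 |

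In the first row the clustered standard errors also agree (0.04206742 in both models for the first dataset). The largest gap is 0.850 vs 0.835. On the log scale that is ln(0.8498/0.8348) ≈ 0.018, against a standard error of about 0.042, or roughly 0.4 of a standard error.

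**4. What the interaction adds.** In the first dataset of the first row, allocation-by-term gives rate ratios of 1.045, 1.084, 0.863, 0.708, 0.597 and 0.606. The main-effect model gives only 0.818. The build-up was put into the data by assumption. The comparison shows which model can display it, and says nothing about what SWIS will do.

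**The case against.** Several counter-arguments have force.

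- **Seasonality is a named aim, and a main effect serves it.** This stands. A reader might infer that the analysis is useless, but it is incomplete for one of two aims.
- **Equality with the primary estimate is conditional.** This stands. A reader might infer that the model must always return the primary estimate. The once-per-child coding under Primary outcome breaks condition (c) if a child with enquiries in two terms is counted in each. Missing periods or a changing student count break (a) or (b). The algebra also covers only school-level log-link counts. The text does not restrict the analysis to s.47, and termly attendance is a student-level linear outcome. There the model still yields one average difference, but the identity has not been shown.
- **Variable delivery is examined elsewhere.** The plan has an allocation-by-fidelity interaction, an analysis excluding intervention schools that never adopted SWIS, a complier average causal effect analysis, and termly surveys. So the documents do not support inferring that variation in delivery goes unexamined. None of these, however, estimates the effect by calendar period.
- **The Discussion's remark that exploratory analyses will matter more.** That remark concerns analyses fed by the process evaluation, most clearly the fidelity analysis. It should not be read as a claim about the term model.
- **This is a condensed article.** Fuller protocol versions exist, and an analysis plan may specify the interaction. It cannot be concluded that the trial lacks one. But the article is not silent here: it states an aim and a model, and uses the word interaction one sentence later where one is meant.

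**Conclusion.** The concern holds in limited form. As worded, the analysis yields a single allocation effect averaged over time, so it cannot address whether the SWIS effect changed across terms. This conclusion does not depend on the three equality conditions. For the school-level count outcomes the allocation estimate is identical to the primary one under those conditions, and otherwise close: within about 0.015 on the rate-ratio scale in the scenarios tried, which rest on the assumed variation in student counts, missingness and repeat risk. No effect size can be attached to what would be missed, because the documents do not say how the effect might vary. A reader might infer that the effectiveness result is weakened. It is not, since the primary estimate, its test and its decision rule do not use this model.

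**What to change.** Amend the sentence in Other secondary analyses along these lines: period-level counts will be modelled with term main effects, to describe seasonality, and with an allocation-by-term interaction, to explore whether the effect changes over time. A pre-specified linear trend or a year-1/year-2 contrast would serve if one interpretable parameter is preferred. Report rate ratios by term and one joint interaction test, labelled exploratory. State that the cluster-robust standard errors already planned will treat all rows from a school as belonging to the same cluster. State also how a child with enquiries in more than one period is counted.

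The cost is a short change of wording. The monthly reporting already planned supplies the data, and the test falls under the Hochberg adjustment already planned for these analyses. The drawback is power, since the trial was sized for the overall rate ratio. On the protocol's inputs a control school expects 925 × 12.6/1000 ÷ 3 ≈ 3.9 enquiries per term, against 925 × 12.6/1000 × 2 ≈ 23.3 over two school years. Term-specific estimates will therefore be imprecise, and a non-significant interaction should not be read as evidence of a constant effect.
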